### Outcome measures

#### Menopause rating scale

The Menopause Rating Scale will be assessed at baseline, week 5, and week 9. The mean change of the Menopause Rating Scale score between baseline and week 5 will be the primary outcome measure of this study.

The Menopause Rating Scale is a self-administered questionnaire developed to measure the severity of menopausal symptoms and their impact on health-related quality of life in aging women [23]. The questionnaire consists of 11 questions in three dimensions including psychological, somato-vegetative, and urogenital aspects [23]. Each item uses a 0–4-point Likert scale. A higher score corresponds to more severe symptoms [23]. Climacteric syndrome is categorized as being mild (5–8), moderate (9–16), or severe (17 and more), according to the total score [24]. The reliability and validity of the Menopause Rating Scale has been confirmed [25] and its Korean version, which is provided by the online Menopause Rating Scale network, will be used in this study [23].

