#### Feasibility assessment

The recruitment rate, completion rate, and medication adherence will be assessed in this trial. The recruitment rate will be presented as a percentage of the total number of registered participants out of the total number of screened subjects. The completion rate will be presented as a percentage of the total number of subjects who completed the study out of the total number of registered participants. The medication adherence will be presented as a percentage of the target dose that was actually taken by the subjects.

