### Participant withdrawal criteria

The subject or the legal representative of the subject withdraws the study participation agreement.A violation of the eligibility criteria is detected during the study period.The occurrence of a serious adverse event makes it difficult to continue the study.A violation of the protocol by a subject.Failure to visit the clinical trial center and receive phone calls during the planned schedule.Taking medications that may affect the result of the trial without the instruction of the investigator during the study period.Inappropriate progress of the study as judged by the investigator.In addition to these cases, when no further medication is required because the symptoms related to climacteric syndrome have disappeared completely or enough to make daily life comfortable, the investigator can decide on early termination of the trial for a subject. In this case, after acquiring the final assessment data, the subject’s participation in the clinical study will be terminated early.

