### Data collection

The investigators at the clinical trial center will obtain written informed consent after explaining the outline of the trial to the potential participants and then screen the eligibility of the participants. For the eligible subjects, baseline characteristics regarding the outcome measures of this study, as well as the social and demographic information and medical background, will then be collected. After randomized group allocation and medication, outcome measures regarding the effectiveness and safety of the intervention will be obtained at weeks 3, 5, and 9. The data will be collected through the patient-reported questionnaires and the participants will be blinded to the group allocation. The results of the questionnaires completed by the subject will be transferred to the clinical report form by the researchers, who are also blinded to the group assignment.

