### Statistical analysis

The statistical analysis will be performed by an independent statistician using SAS® version 9.4. When the demographic and sociological data of the subjects are continuous, they will be presented in the form of means and standard deviations. Differences between the two groups will be analyzed using Student’s *t* test (or the Wilcoxon rank sum test). Categorical data will be presented in frequencies and percentages and analyzed using the chi-square test (or Fisher’s exact test). The missing values will be processed using the multiple imputation method.

The full analysis set will be the main analysis set, and the per-protocol set will be supplementary. The full analysis set will be used to achieve the ideal intention-to-treat principle as completely as possible. It will include all randomized participants unless the following criteria are met: the eligibility criteria are not met, the test drug has not been taken, or data cannot be collected because the participant was never evaluated after random assignment. The per-protocol set will include the participants who have completed the study without any major protocol violations.

The analysis of covariance will be performed to analyze the between-groups differences of the primary and secondary outcome measures. The dependent variables will be the values acquired after intervention, the covariate will be the baseline value, and the fixed factor will be the group. A small group analysis will also be performed to explore the differences in the effect of DJS among the peri- and postmenopausal participants.

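### Exit for good response ends study participation, not only the medicine, so good responders can leave before the week-5 primary assessment with only an off-schedule score

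*Protocol article*

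**What the plan says.** The Participant withdrawal criteria end with a separate rule for women who do well. If no more medicine is needed because climacteric symptoms have gone, or have eased enough for comfortable daily life, "the investigator can decide on early termination of the trial for a subject". Final assessment data are taken, and then the subject's "participation in the clinical study will be terminated early". The rule gives no MRS threshold and no earliest time.

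The endpoint is fixed in time: "The mean change of the Menopause Rating Scale score between baseline and week 5 will be the primary outcome measure of this study". On the schedule, the Menopause rating scale section states: "The Menopause Rating Scale will be assessed at baseline, week 5, and week 9". The other efficacy measures (WHOQOL-BREF, Blood Deficiency Scoring System, hormones, lean body mass) have the same three time points. The Data collection section says that "outcome measures regarding the effectiveness and safety of the intervention will be obtained at weeks 3, 5, and 9", but it does not say that the MRS is among the week-3 measures.

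On analysis, the full analysis set is the main set, and "The missing values will be processed using the multiple imputation method". The supplementary set is narrower: "The per-protocol set will include the participants who have completed the study without any major protocol violations". For feasibility, "The completion rate will be presented as a percentage of the total number of subjects who completed the study", with registered participants as the denominator.

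**The concern.** The trigger for leaving is improvement in the same symptoms that the primary outcome measures. If DJS works, more women on DJS than on placebo will meet it. Blinding prevents deliberate selection by arm, but it does not equalise how often a response-based rule is met. The week-5 value therefore goes missing because of the outcome, and at different rates in the two arms.

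An analysis plan can choose how to handle the missing value, but it cannot recover week-5 and week-9 observations that the withdrawal rule stops from being collected. The effect estimate and the feasibility rates of this pilot are meant to inform a full-scale trial, so distortion in either carries forward.

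**Working it through.** **Timing.** Treatment lasts 4 weeks, visits are every 2 weeks, and the post-treatment evaluation is at week 5 (Study design; Interventions). A rule that turns on medicine no longer being needed can apply only while medicine is being given, that is, before week 5. The one scheduled visit in that window is week 3.

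**What imputation can do.** A woman who exits at about week 3 has an MRS score at a time when, on the schedule in the Menopause rating scale section, the women who stay have none. The link from exit score to week 5 then cannot be estimated from the data. If the week-3 measures mentioned under Data collection include the MRS for every woman, it can be.

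**Plan's own figure.** Sample size section: means 10.8 and 2.16, difference 8.64, SD 8.012, alpha 0.05 (two-sided reproduces the result), power 0.8.

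n = 2 × (1.960 + 0.842)² × 8.012² / 8.64² = 13.5, so 14 per group; 14 / 0.85 = 16.5, so 17. The stated figures reproduce. The concern does not depend on them, but the same means and SD are used below.

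**Illustration of size.** These assumptions are not in the documents: week-3 mean change is 60% of week 5; week-3 SD is 0.8 × 8.012 = 6.41; correlation between week 3 and week 5 is 0.7; a woman is eligible for exit if she has improved by more than 10 points at week 3.

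Write μ for the week-5 mean change, m = 0.6μ, z = (10 − m)/6.41 and p = 1 − Φ(z). In the triggered women, the contribution to the week-5 mean is A = μp + 0.7 × 8.012 × φ(z), and the contribution of their exit scores is B = mp + 6.41 × φ(z).

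| | m | z | p | A | B |
|---|---|---|---|---|---|
| DJS | 6.48 | 0.549 | 0.291 | 5.07 | 4.09 |
| Placebo | 1.296 | 1.358 | 0.087 | 1.08 | 1.13 |

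If a share q of triggered women is terminated, an arm's mean is (μ − qA)/(1 − qp) when exit scores are not used, and μ − qA + qB when they stand in for week 5.

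- q = 1: loss 29% DJS and 9% placebo. Not used: 8.08 − 1.19 = 6.9. Substituted: 9.82 − 2.21 = 7.6.
- q = 0.5: loss 15% and 4%. Not used: 9.67 − 1.69 = 8.0. Substituted: 10.31 − 2.19 = 8.1.

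Simulation with 300,000 women per arm agrees (6.87 and 7.60; 7.98 and 8.13). When week-3 scores exist for all women and enter the imputation, it returns 8.63 to 8.64, so the bias disappears.

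**Sensitivity.**

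- Grid of 81 scenarios (week-3 response 40% to 80%, correlation 0.5 to 0.85, trigger 10 to 15 points, 25% to 100% terminated): 5.4 to 8.6 with exit scores not used, 7.4 to 8.8 with them substituted.
- A separate model (week-3 SD equal to 8.012, response 50% to 100%, correlation 0.5 to 0.9, trigger 12 or 16 points, all triggered women leaving): exits 9% to 44% on DJS and 3% to 11% on placebo; 5.1 to 8.2 among those who stay, 7.7 to 9.5 with exit scores substituted.

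The values clearly above 8.64 occur where the week-3 response is high.

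**Feasibility.** If such a woman counts as a non-completer, completion falls by 1/34 = 2.9 percentage points. If the target is all 3 × 28 = 84 doses, a stop at the week-3 visit after 3 × 14 = 42 doses gives her 50% adherence and takes 50/34 = 1.5 points off the trial mean.

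**The case against.** The strongest reply is that the rule may rarely be used and its effect is modest. It is discretionary and blinded, and only one scheduled visit falls before week 5. With a 15-point trigger and half terminated, the same model gives about 4.6% exits on DJS, under one woman of 17. A final assessment is required, so the estimates that leave it out discard data the protocol collects. With the exit score used, the base-case shift is 0.5 to 1.0 points, against a planned standard error of 8.012 × √(2/17) = 2.75, or about 0.2 to 0.4 of a standard error, and its sign is not fixed. The simulated trigger is a change score, whereas the protocol's trigger is residual state: a woman who falls from 22 to 12 would meet the former and still be rated moderate. The effects on completion, adherence and the per-protocol set rest on readings the article does not state.

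Much of this stands as a limit on size. The frequency of exits is unknown, the shift is small against sampling error in a trial of 34, and the feasibility effects are conditional. It does not remove the defect. An exit score taken early is not the week-5 endpoint, and nothing says it is to be treated as one. Week 9 is lost on any reading. A trigger set on residual symptoms also gave attenuated estimates, 7.4 to 8.5. A week-3 MRS in all women would allow sound imputation of week 5, but the Menopause rating scale section points the other way.

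**Conclusion.** The concern holds, as a should-fix point with medium confidence. The rule as written ends follow-up because of the outcome, before the primary time point, and more often in the better arm. Under the base assumptions the true 8.64 is estimated as 8.1 to 7.6 with the exit score and 8.0 to 6.9 without it. If exit scores are not used, the bias is toward no effect. If they are substituted, that direction is likely but not certain, because a response largely complete by week 3 can reverse it. All of these sizes rest on assumed week-3 response, correlation, trigger and termination rate. The loss of the scheduled week-5 and week-9 observations does not: it follows from the text. The effects on completion, adherence and the per-protocol set depend on how early exits are classified, which the article does not say.

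**What to change.** Amend the withdrawal rule so that the investigator may stop study medicine for improvement while the woman stays in the study. Collect the MRS and the other outcomes at weeks 5 and 9 as scheduled, and analyse them as observed in the full analysis set. Count a woman who attends these visits as a completer, and report medicine stopped for improvement separately from non-adherence.

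The cost is a short amendment and two already planned visits for a few women. The clinical decision on medicine is unchanged. Recruitment was under way when the article was published, so the amendment protects data only from women who have not yet left under the current rule.

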### Sample size

In a previous study [11], the mean change in the Menopause Rating Scale score was 10.8 after 30 days of DJS administration. Based on a preliminary study similar to ours [12], we assumed that the Menopause Rating Scale score of the placebo-treated group will change by 2.16, which is 20% of the mean difference of DJS group. Therefore, the mean difference between the Menopause Rating Scale scores of the DJS group and the placebo group is calculated to be 8.64. The standard deviation is estimated to be 8.012 according to the data acquired from the DJS-treatment group in the previous study [11]. Under this assumption, the required sample size was calculated to be 14 per group, with a significance level of 0.05 and a power of 0.8. Considering a dropout rate of 15%, 17 people are ultimately required per group.

### Data collection

The investigators at the clinical trial center will obtain written informed consent after explaining the outline of the trial to the potential participants and then screen the eligibility of the participants. For the eligible subjects, baseline characteristics regarding the outcome measures of this study, as well as the social and demographic information and medical background, will then be collected. After randomized group allocation and medication, outcome measures regarding the effectiveness and safety of the intervention will be obtained at weeks 3, 5, and 9. The data will be collected through the patient-reported questionnaires and the participants will be blinded to the group allocation. The results of the questionnaires completed by the subject will be transferred to the clinical report form by the researchers, who are also blinded to the group assignment.

### Statistical analysis

The statistical analysis will be performed by an independent statistician using SAS® version 9.4. When the demographic and sociological data of the subjects are continuous, they will be presented in the form of means and standard deviations. Differences between the two groups will be analyzed using Student’s *t* test (or the Wilcoxon rank sum test). Categorical data will be presented in frequencies and percentages and analyzed using the chi-square test (or Fisher’s exact test). The missing values will be processed using the multiple imputation method.

The full analysis set will be the main analysis set, and the per-protocol set will be supplementary. The full analysis set will be used to achieve the ideal intention-to-treat principle as completely as possible. It will include all randomized participants unless the following criteria are met: the eligibility criteria are not met, the test drug has not been taken, or data cannot be collected because the participant was never evaluated after random assignment. The per-protocol set will include the participants who have completed the study without any major protocol violations.

The analysis of covariance will be performed to analyze the between-groups differences of the primary and secondary outcome measures. The dependent variables will be the values acquired after intervention, the covariate will be the baseline value, and the fixed factor will be the group. A small group analysis will also be performed to explore the differences in the effect of DJS among the peri- and postmenopausal participants.

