## Methods/design

### Study design

This is a randomized, parallel-group, double-blind, placebo-controlled pilot clinical trial. Placebo or DJS will be randomly assigned, with a 50% probability, to the subjects who have provided written consent and passed the screening criteria for this study. The treatment period will be 4 weeks. Post-treatment evaluations will be performed at week 5, and then follow-up evaluations will be conducted at week 9. The study schedule is summarized in Figs. 1 and 2.

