### Randomization and allocation concealment

A statistician will generate a random allocation list using Strategic Applications Software (SAS®) Version 9.4 (SAS institute. Inc., Cary, NC, USA). The list will assign 34 subjects to one of two groups, coded A or B. The list with the random allocation codes will be sealed in an opaque envelope and stored in a double-locked cabinet.

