#### Hormone test

For an objective understanding of the menopausal situation, the concentrations of follicle-stimulating hormone and estradiol in blood samples will be measured. The hormone test will be conducted at baseline, week 5, and week 9. The blood specimen will be sent to the clinical pathology department for analysis.

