One characteristic of this study is that it is designed based on pattern identification, a theory of diagnosis and a therapeutic system that is unique to traditional East Asian medicine. Danggwijagyaksan has been used predominantly in patients who are identified as having blood-deficiency patterns under this system. Therefore, this study will only include patients who have been identified as having a pattern of blood-deficiency using the Blood Deficiency Scoring System questionnaire in the screening phase. We are working on another pilot study to evaluate the efficacy and safety of Gyejibongnyeonghwan (also called Guizhifulingwan or Keishibukuryogan in China and Japan) for the treatment of climacteric syndrome in peri- and postmenopausal women who are diagnosed with blood stasis patterns under the pattern identification system [12]. A series of these studies involving the unique theory of traditional medicine is expected to provide a basis not only for the efficacy and safety of the herbal medicine for the treatment of climacteric syndrome but also for the means of applying the old and historical concepts of traditional medicine in East Asia in clinical settings today. It is expected that the results of these studies will be able to provide basic data to guide physicians or traditional medical doctors at clinics more clearly in prescribing candidate herbal drugs, such as DJS or Gyejibongnyeonghwan, for patients with climacteric syndrome.

The first limitation of this study is that the primary outcome measure is the Menopause Rating Scale, which is entirely dependent on the participants’ subjective assessments. To compensate for this problem, we will also measure the levels of female hormones, such as follicle-stimulating hormone and estradiol, as objective indicators of changes in the menopausal condition.

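### One baseline-plus-group ANCOVA is fixed for every outcome, without menopausal status and with no scale named for the hormones: valid, but probably inefficient for estradiol

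*Protocol article*

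**What the plan says.** Under Statistical analysis, one model covers all efficacy outcomes: "The analysis of covariance will be performed to analyze the between-groups differences of the primary and secondary outcome measures". Its parts are listed: "The dependent variables will be the values acquired after intervention", and "the covariate will be the baseline value, and the fixed factor will be the group". The same section adds: "A small group analysis will also be performed to explore the differences in the effect of DJS among the peri- and postmenopausal participants".

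The inclusion criteria admit peri- and postmenopausal women, with natural or induced menopause. Randomization is described without strata: "The list will assign 34 subjects to one of two groups, coded A or B" (Randomization and allocation concealment).

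Under Hormone test, "the concentrations of follicle-stimulating hormone and estradiol in blood samples will be measured" at baseline, week 5 and week 9. The Discussion names reliance on self-report as a limitation of the primary scale and offers the hormones in compensation, "as objective indicators of changes in the menopausal condition".

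**The concern.** The list of model terms reads as complete, and status is not in it, although the plan itself treats status as a possible modifier of the effect. With 34 women and no described stratification, the arms can differ noticeably in their share of perimenopausal women, and whatever the baseline value does not absorb then stays in the residual error.

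The hormones add a question of scale. If estradiol is right-skewed and higher in perimenopausal women, a few large values dominate a least-squares fit on untransformed data. The hormones are meant to be the objective counterweight to a subjective primary outcome, so an inefficient model there weakens the one check the plan offers. The sample size is fixed, so the choice of model is one of the few ways left to gain precision.

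Finally, the planned peri/post question is about a difference in effects. The listed terms do not by themselves produce an estimate of that difference.

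**Working it through.** **1. The plan's own figure.** Sample size section: difference 8.64, SD 8.012, alpha 0.05 (two-sided), power 0.8. n per group = 2 × [8.012 × (1.960 + 0.842) / 8.64]² = 13.5, so 14. With 15% dropout, 14 / 0.85 = 16.5, so 17. Both stated figures reproduce. They concern the Menopause Rating Scale (MRS) only; the hormones were not used to size the trial.

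**2. What this size can detect.** By the noncentral t distribution, 80% power needs a standardized difference of 1.10 with 14 per group and 0.99 with 17, before any gain from the baseline covariate. Low power for secondary outcomes therefore comes first from the sample size.

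**3. Chance imbalance in status.** If allocation is unstratified with 17 per arm and K of the 34 women are perimenopausal (K is assumed; the article gives no split), the count in one arm is hypergeometric. The probability that the arms differ by 4 or more is 0.259 for K = 10, 0.282 for K = 12 and 0.296 for K = 14.

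**4. Estradiol, raw against log scale.** The article gives no mean, SD, skewness or peri/post gap, so every input here is an assumption. Log-normal baseline and follow-up values were simulated, with a multiplicative treatment effect and a two-sided 5% test of the group term.

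Milder set: 14 per group, half perimenopausal, between-woman log-SD 0.4, true 1.5-fold effect, 2,000 trials per row.

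| Peri/post gap (log units) | Within-woman log-SD | Raw | Log | Log + status |
|---|---|---|---|---|
| 1 | 0.3 | 57% | 71% | 74% |
| 1 | 0.5 | 26% | 37% | 41% |
| 2 | 0.3 | 43% | 69% | 73% |
| 2 | 0.5 | 18% | 33% | 39% |

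From the unrounded results, the log scale gains 11 to 26 points and status a further 3 to 6.

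More skewed set: 17 per arm, 40% perimenopausal, medians 60 and 10, log-SDs 1.0 and 0.6, two-fold effect.

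| Baseline/follow-up correlation | Raw | Log | Log + status |
|---|---|---|---|
| 0.3 | 19% | 61% | 72% |
| 0.5 | 24% | 75% | 80% |
| 0.7 | 35% | 91% | 92% |

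The log scale gains 42, 51 and 56 points; status adds 11, 5 and 1. With 15 per arm and correlations from 0.3 to 0.9, raw power runs from 19% to 62% and log power from 57% to 100%. Under milder assumptions and a 1.5-fold effect at that size, the ranges are 49% to 99% raw and 63% to 100% log.

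With no effect, the raw baseline-plus-group model rejected in 3.7% to 4.6% of trials in the milder set and in about 3% in the more skewed set. It is conservative, not invalid.

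**5. FSH.** Under an assumed left-skewed distribution and a 1.5-fold fall, log-scale power was 47% to 99% against 56% to 100% on the raw scale. The log scale gained nothing.

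**6. Status in the MRS model.** With 14 per group, power is 78% if status explains none of the residual variance, and 80% to 86% if it explains 5% to 20%. These shares are assumptions.

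**7. The peri/post interaction on the MRS.** SE = 8.012 × √[2/(17f) + 2/(17(1−f))], where f is the perimenopausal share.
- f = 0.5: 8.012 × √0.471 = 5.50
- f = 0.2: 8.012 × √0.735 = 6.87
- Main effect, for comparison: 8.012 × √(2/17) = 2.75

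The interaction SE is thus 2.0 to 2.5 times that of the main effect. With 34 women, 80% power needs an interaction of 15.9 to 19.9 points. Power for one as large as the whole assumed effect (8.64) is 23% to 33%.

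**The case against.** Baseline-adjusted ANCOVA is a standard and valid choice. Naming post-treatment values as the dependent variable separates them from change scores; it neither prescribes nor forbids a transformation. Transformations and distribution checks are commonly left to a statistical analysis plan, which is not shown. That stands: a reader might infer that the plan commits to raw hormone values, but the article only names no scale.

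A reader might also infer that the subgroups will be fitted separately with no interaction estimate. The article does not say so. It states the aim of exploring differences in effect and leaves the method open.

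A third tempting reading is that chance imbalance in status biases the comparison. It does not: randomization keeps the group comparison unbiased without status, and the baseline value already carries part of any status difference. Status adds little once the log scale is used, and nothing in the documents shows that it predicts MRS change.

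The low power for hormones is mainly a matter of 14 to 17 women per group in a pilot whose Discussion concedes that it is small. That also stands, but the raw/log gap arises at the same sample size, so it does not remove the point. The list of model terms is a stated choice, and a better one is available from data already collected.

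**Conclusion.** The point holds as a minor efficiency improvement. The stated model leaves out a factor that the plan itself considers relevant, and names no scale for outcomes whose distribution may make the scale matter. Under log-normal estradiol that differs by status, the cost of the raw scale is about 10 to 55 points of power for a 1.5- to 2-fold effect, except where power is already near 100%; status is worth about 0 to 11 points. The direction held in every estradiol scenario of that size that was not saturated. The size depends on the assumed spread, peri/post gap and baseline correlation, none of which the documents give.

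The documents and calculations do not support extending this to FSH, calling the primary comparison biased, or saying that error rates are inflated.

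**What to change.** In the analysis section, or in the analysis plan before unblinding:

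- Add menopausal status (peri/post) as a fixed factor in the ANCOVA models for the primary and secondary outcomes.
- Analyse estradiol on the log scale, with log baseline as covariate, and report the ratio of geometric means with its 95% CI.
- For FSH, choose the scale from blinded data and record the choice before unblinding.
- Report the planned peri/post comparison as a group-by-status estimate with its 95% CI, labelled exploratory.

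The cost is wording and one degree of freedom for status, with one more in the interaction model. No new data are needed. The interaction interval will be wide: with 29 degrees of freedom its half-width on the MRS is about 2.045 × 5.50 = 11 to 2.045 × 6.87 = 14 points, so it can inform the next trial but cannot settle whether the effect differs.
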